#### Post-field test debriefing interviews

Once post-test measures are completed, the RC will conduct a brief, semi-structured follow up debriefing interview with each participant, focusing on the experience of using the decision support tool; this will also be conducted via telephone. These interviews will be conducted according to a semi-structured patient interview guide we have developed based on the OMRU knowledge translation framework. This guide will solicit participants’views about the impact of their values on decsions made, changes that may have occurred in treatment-related preferences and perceptions of risks/benefits, general reflections on the decision making process, applicability and usefulness of the decision support tool in context (e.g. barriers, facilitators to use), and their level of comfort interacting with the HCPs when using the tool. For efficiency of data collection, the RC will conduct a similar debriefing with our site HCPs in the form of focus groups; one focus group per site will be conducted. A semi-structured HCP focus group interview guide will also be used, also based on OMRU. These discussion questions will target HCPs’ views of the applicability and utility of the decsion support tool in their respective practice contexts, perceived efficacy of the tool in assisting their patients to arive at treatment-related decions, and perceived enablers and facilitators to decision tool implementation. The RC will take field notes, and these sesions will be audio-taped and transcribed verbatim, in preparation for qualitative content analyses.

#### Instrumentation: pre/posttest measures

##### Acceptability questionnaire

Decision support tool acceptability will be assessed using the Decision Aid Acceptability Questionnaire [32], comprised of open and closed-ended questions. Closed-ended questions will elicit feedback on amount of content, clarity, and helpfulness of the PtDA, acceptability of format, whether the information was presented in a balanced and fair manner, user satisfaction, and whether users would recommend it to other RFA patients. Evidence supports the validity of the Decision Aid Acceptability Questionnaire [32].

##### Decisional conflict scale

The Decisional Conflict Scale (DCS) [48] will be used to measure the primary effectiveness outcome of decisional conflict [49,50]. The purpose of this scale is to measure a person’s perception of difficulty in making a decision including, perceived uncertainty in choosing between options; modifiable factors contributing to uncertainty such as feeling uninformed, unclear about personal values, and unsupported; and quality of the choice selected. Choice quality is defined as choice that is informed, consistent with personal values, and personally satisfying satisfaction [32,48]. The DCS consists of 16 items. Scoring involves the summation and averaging of the items, ranging from 1 (low decisional conflict) to 5 (high decisional conflict). Scores of 2.0 or lower are associated with those who make decisions; scores of 2.5 or greater are associated with those who delay decisions [48]. The DCS has been used to assess health-related decisions across divergent health conditions and contexts [32,48]. Test-retest and internal consistency coefficients exceed 0.78. This scale varies in its ability to discriminate between different decision-supporting interventions [32,48].

##### Knowledge/comprehension test

Knowledge of RFA treatment options will be assessed using a knowledge questionnaire developed for this study. We will use a standardized, validated format developed by Metcalfe et al. [32] that includes items regarding the mechanisms of action and effectiveness of various (RFA) treatment options, as well as known possible adverse effects. Effectiveness estimates will be presented in the form of a continuous scale from 0 to 100%. Content knowledge items will be presented as ‘true’ or false’; these items will be developed as part of our consensus conference.

##### Choice predisposition tool

Participants’ decision predispositions will be measured using the Choice Predisposition Tool [15,32]. Participants will be asked to mark along a 15-point scale anchored by ‘not leaning towards’ or ‘leaning towards’ particular treatment options (e.g. Spinal cord stimulation, enhanced external counter-pulsation); a response option in the middle indicates ‘unsure’. Test-retest reliabilities of various iterations of this scale, across populations, exceed 0.90; they are also consistently correlated with personal values and expectations, and sensitive to change [15,32].

#### Data management and analyses

All electronic and audio-taped data will be secured in a locked facility. To inform sample size calculations and data analysis feasibility for a larger trial, data will be analyzed as in a larger study, and estimates of variance and correlation (i.e. intracluster correlation within site) will be generated. All quantitative data collected will be checked for departures from normality and analyzed initially with descriptive statistics; measures of central tendency and dispersion (e.g. means and standard deviations) will be computed for continuous variables. For categorical demographic variables, frequencies and proportions will be reported. Differences between pre and post-intervention measures will be examined using paired t-tests for all interval scaled measures, provided the assumption of normality is met [51]. Where the normality assumption is violated, the non-parametric Wilcoxon signed-rank test will be used [51].

As this protocol focuses on appropriateness, acceptability and pilot testing of the PtDA, no sub-analyses were planned to examine the influence of participant characteristics such as age, sex, and highest level of formal education on the outcomes of decisional conflict, knowledge of treatment items, and choice predisposition. Examination of the influence of participant characteristics will be undertaken in a subsequent effectiveness RCT.

An examination of missing data will be of particular importance to the pilot analysis. The level and pattern of missing data will be quantified. Presence versus absence of data for each scale will be compared across demographic and clinical characteristics to identify particular groups of individuals that may have a higher propensity for missing data.

All transcribed qualitative data, including needs assessment data, HCP-participant visits, participant follow-up interviews, and HCP focus groups will be analyzed using inductive thematic qualitative content analysis [52-54]. The frequency, extensiveness, and specificity of comments will guide data categorization into recurrent themes [52-54]. These themes will be altered and refined through a recursive process from the data to analyst-generated categorical and conceptual definitions.

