### Patient decision aids

According to the International Patient Decision Aids Standard (IPDAS) collaboration [12,13] patient decision aids (PtDAs) are evidence-based tools designed to help people engage in deliberative treatment-related decision making by providing information on the options and outcomes relevant to health status. These tools are used to supplement, not replace, consultation between health care professionals (HCP) and patients [12,13]. In so doing, PtDAs help individuals to understand the range of options available and the probable consequences of various treatment options [12,13]. When designed optimally, PtDAs also distill for patients they value they place on the potential consequences of treatment approaches (e.g. invasive, non-invasive).

A recent (2011) Cochrane review of 86 studies [14] found that relative to routine health professional counseling, PtDAs improve patients’ knowledge of treatment options and perception of outcome probabilities, as well as their level of involvement in shared decision making. Ideally, effective PtDAs express outcome probabilities in both visual and written form to communicate absolute risk or benefit clearly to patients (i.e., X people out of 100) [15]. There is general consensus that decision support tools do not include passive informed consent materials, educational interventions not geared to a specific decision, or interventions designed to promote compliance with a recommended option rather than a choice on personal values [16,17]. Decision support tools have been developed in a range of formats including decision boards, interactive videodiscs, personal computers, audio-tapes, audio-guided workbooks, pamphlets, and group presentations [14].

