#### Primary purpose

The primary purpose is to determine the appropriateness and acceptability of the PtDA for our key effectiveness outcomes including decisional conflict (*primary outcome*) and knowledge of treatment options, and choice predisposition (*secondary outcomes*). This pilot test will allow us to determine the effect size of the PtDA, which will inform the required sample size for a randomized controlled trial (RCT) of the effectiveness of the tool as an intervention.

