#### Field test procedure and outcomes

As an integrated KT strategy involving stakeholders from the inception of this project, Pilot 2 site co-investigators and collaborators are assisting us to establish site-designated HCPs, who will assist us with recruitment. These HCPs will be oriented to the study and procedures for pilot testing the PtDA during scheduled visits with their patients enrolled in the study. Potentially eligible patients, identified by these HCPs, will be asked if they would be willing to speak to the RC about the study. If verbal consent is obtained, contact information will be sent to the RC via telephone. The RC will then phone the referred individual to confirm eligibility, provide a detailed study explanation, and obtain preliminary verbal consent. Eligible patients agreeing to participate will be asked for baseline demographic information via phone interview. They will receive the study explanation, and two copies of the consent form; a postage-paid, addressed envelope will be included to return one signed consent form to the RC. Approximately 1 month prior to their scheduled visits with a site-designated HCP, the RC will conduct pre-test data collection via telephone interview, using our pre/post-test questionnaires. These instruments are designed to assess knowledge about treatment options, decisional conflict, and predisposition about treatment options. Upon completion of baseline data collection, the RC will mail participants a copy of the decision support tool. Participants will be asked to review the decision support tool and arrangements will be made for them to complete the PtDA Acceptability Questionnaire via telephone with the RC.

A paper-based version of the decision support tool will be implemented during participants’ scheduled visits with their site-designated HCPs. Where permission is granted (by participants and site-HCPs), the RC will make arrangements for these sessions to be audio-taped and later, transcribed verbatim. While discussing/deliberating treatment options, participants will be encouraged to share their thoughts on the decision support tool, ask questions about the available RFA treatment options, and discuss any concerns that they may have. This iterative approach supports the interactive principles of integrated knowledge translation [45-47]. One week following these scheduled visits, the RC will conduct post-test outcome assessment via telephone interviews, using our pre/post-test questionnaires.

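### Choice predisposition is a two-sided scale centred on 'unsure', but the only stated pre/post test measures net signed shift, so opposite moves off 'unsure' cancel

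*Protocol article*

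**What the plan says.** Under 'Primary purpose', the protocol article makes decisional conflict the primary effectiveness outcome, and knowledge and choice predisposition secondary outcomes.

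Predisposition is collected by telephone before the aid is mailed and again one week after the clinic visit. Of the pre/post questionnaires, 'Field test procedure and outcomes' says: "These instruments are designed to assess knowledge about treatment options, decisional conflict, and predisposition about treatment options".

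'Choice predisposition tool' gives the format: "Participants will be asked to mark along a 15-point scale anchored by" not leaning and leaning towards particular options, and "a response option in the middle indicates" that the patient is unsure.

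'Data management and analyses' has one rule for pre/post change: "Differences between pre and post-intervention measures will be examined using paired t-tests for all interval scaled measures, provided the assumption of normality is met". The fallback is: "Where the normality assumption is violated, the non-parametric Wilcoxon signed-rank test will be used". No separate summary is given for predisposition.

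On direction, 'Patient decision aids' excludes from decision support tools "interventions designed to promote compliance with a recommended option rather than a choice on personal values". 'Values clarification' has patients weigh each option by their own values before stating a leaning. 'Phase 3: Pilot test 2' lists, among the known effects of such aids, change in initial inclinations once risks are accurately perceived. None of these names a direction.

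**The concern.** A paired t-test on the raw score asks whether the group, on average, moved towards or away from an option. The signed-rank test asks much the same question. Neither asks whether individuals moved off 'unsure'. If an aid helps patients settle according to their own values, some will settle for an option and others against it, and those changes have opposite signs.

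The risk is in interpretation. A mean change near zero could be reported as no effect on predisposition when most patients had changed. The pilot is also meant to supply effect size estimates for a later randomised trial, with data analysed as in a larger study. A signed near-zero estimate would then go forward as the description of this outcome.

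**Working it through.** **The plan's own figure.** The only power statement concerns decisional conflict: n = 20, alpha 0.05, power 0.80, SD 0.81, pre-post correlation 0.80, detectable difference 0.34. SD of differences = 0.81 × √(2 × (1 − 0.80)) = 0.512. A two-sided paired t-test then detects 0.338, with power 80.4% at 0.34. The figure reproduces. Nothing comparable is given for predisposition.

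**Exact example.** Code the scale 1 to 15, so 'unsure' is 8 (an assumption, since the article gives no coding). Let 20 patients start at 8; ten end at 12 and ten at 4.
- Signed change: (10 × 4 + 10 × (−4)) / 20 = 0, so t = 0 and p = 1.
- Change in distance from the midpoint: |12 − 8| − 0 = 4 and |4 − 8| − 0 = 4, so +4 for every patient.

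**How cancellation depends on the split.** If each patient moves m points and a share p moves towards the option, then before rounding and truncation
- mean signed change = m(2p − 1)
- SD of change = √(4m²p(1 − p) + s²), where s is the noise SD.

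With m = 4, s = 1.5 and n = 20:
- p = 0.5: mean 0.
- p = 0.7: mean 1.6, SD √(13.44 + 2.25) = 3.96, mean / (SD/√20) = 1.81.
- p = 0.9: mean 3.2, SD √(5.76 + 2.25) = 2.83, mean / (SD/√20) = 5.06.

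**Simulation.** 20,000 pilots of 20 patients, scores rounded and held to 1–15, 4-point moves. The document gives no inputs for this scale, so two assumed sets were used: A has baseline SD 2.5 and noise SD 1.5; B has baseline SD 2 and noise SD 1. Entries are rejection rates at two-sided 0.05; the Wilcoxon column rests on 2,000 pilots.

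| Share moving towards the option | Signed t, A | Signed t, B | Wilcoxon, B |
|---|---|---|---|
| 50% | 5% | 5% | 5% |
| 60% | 14% | 14% | 12% |
| 70% | 40% | 43% | 36% |
| 80% | 77% | 80% | 71% |
| 90% | 98% | 99% | 96% |

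The fallback cancels in the same way. At an even split, the signed t-test also stays at about 5% for 3-point and 5-point moves under both sets. A t-test on the change in |score − 8| rejects in about 87% (A) and 97% (B) for 4-point moves, whatever the split.

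**Limits of the distance measure.**
- *Reversals.* With baseline around 11 (SD 1.5), every patient moving 6 points down and noise SD 1.5, the signed test rejects in about 100% and the distance test in about 5%.
- *Noise.* With no true effect and noise added only at post-test (set A), the distance test rejects in 17 to 18%. With equal noise at both times it rejects in about 5%.

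The 87% and 97% figures therefore show that the two statistics answer different questions. They do not show that distance is better throughout.

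**The case against.** The best defence is that the signed change has a proper role. 'Phase 3: Pilot test 2' treats a change of inclination after risks are understood as a benefit of decision aids, and the debriefing interviews ask about changed preferences. If patients share a misperception, a common shift is what one would look for, and the signed mean measures it. Distance from the midpoint would miss it when patients cross from one side to the other. This stands, and it rules out replacing the signed analysis.

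Three stronger readings are tempting, and the documents do not support them:
- *A significant signed change means the aid steers patients.* It could equally be a shift after risks are correctly understood, which the protocol counts as a benefit.
- *A working aid would look inert.* The primary Decisional Conflict Scale runs in one direction, from low to high conflict, and covers uncertainty in choosing. Resolved uncertainty can show there.
- *The same cancellation affects the 0–100% effectiveness items in the knowledge test.* The article does not say raw estimates are averaged, and it refers to a validated format that is not shown.

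It is also fair to say that an even split is the worst case, that the planned descriptive statistics include dispersion and would show scores spreading (in set A the SD rises from about 2.5 to about 4.5), and that the analysis section does not name this scale. But the rule covers all interval-scaled measures, the fallback behaves alike, and no other pre/post rule is given. A wider SD hints at divergence without showing who moved off 'unsure'.

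**Conclusion.** The point holds in limited form. The stated test suits one question about predisposition, net shift, and cannot answer whether patients moved off 'unsure'. A null signed result would not show that the aid left predisposition unchanged. The size depends on the split of directions, which the document does not give: cancellation is complete at 50/50, substantial at 70/30 (about 40% rejection) and almost gone at 90/10 (about 98%). These figures rest on assumed coding, baseline spread, noise and 4-point moves in 20 patients. The consequence is limited to one secondary outcome in a single-group pilot and leaves the primary outcome and its sample size statement untouched.

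**What to change.** In 'Data management and analyses', add a rule for choice predisposition. For each treatment option:
1. As the main summary, a pre/post cross-table of not leaning, unsure and leaning, with the scale points in each category fixed in advance.
2. Beside it, the mean change in distance from the midpoint with a 95% CI.
3. The signed mean change, kept and labelled as the net shift in inclination.

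State that the distance measure is not to be read alone, because it misses reversals and can rise if post-test scores are noisier. The cross-table shows the reversals.

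The cost is analysis wording and somewhat more output. No new data are needed, since the scale is already planned at both times. 'Study status' puts enrolment at Pilot 1, so the rule can be set before Pilot 2 data exist.

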## Discussion

This paper describes the protocol for the development and pilot testing of a PtDA for those who suffer RFA. A number of RCTs to date have examined the effectiveness of PtDAs in specific cardiac populations such as ischemic heart disease [55], newly diagnosed hypertension [56] and/or dyslipidemia [57], atrial fibrillation [58], and those referred for diagnostic coronary angiography [59]. The results of these primary trials corroborate with those of the 2011 Cochrane review [14]. Consistent improvements were found in patients’ knowledge of their conditions and available treatment options [56-59], decisional conflict and perceptions of potential outcome improvements and relative risks, and perceived levels of patient autonomy in the shared decision making process [55]. One RCT also found that engagement with a PtDA did not increase participants’ state anxiety [56], suggesting that informing cardiac patients about potential treatment risks, and addressing their preferences does not impose added psychological burden. In a RCT of a PtDA to augment pharmacist consultation about lipid lowering and/or antihypertensive pharmacotherapies, no impact on patients’ knowledge or risk perception was found [57]. However, clinician-patient interactions with the decision tool were brief and the complexity of the tool may have been a contributing factor [57].

While a PtDA has been designed specifically for angina [60] this tool targets therapies for chronic stable angina and unstable angina, two conditions which, unlike RFA, are amenable to standard medical therapies. Moreover, we found that this tool did not meet the internal quality and impact standards set forth by the IPDAS [18], receiving scores of 5/9 and 0/2 for development process and effectiveness criteria, respectively [33].

A decision support tool for RFA is needed and the available data suggest that by developing such a tool, we may be able to help RFA sufferers better understand their condition and the effectiveness of available treatment options (in their respective clinical settings) as well as their implications (e.g. risks vs. benefits). By virtue of this tool, we may also be able to facilitate identification and inclusion of patients’ values and preferences in the decision making process. This is particularly important as RFA is an intractable condition, necessitating that the selected course of treatment be lifelong [1,2,5,6].

This study will yield a much needed PtDA for people living with RFA and pilot data to support a subsequent effectiveness study.

### Study status

Phase 1 is complete and participants are currently being enrolled in Pilot 1.

## Abbreviations

CPG: Clinical practice guideline; DCS: Decisional conflict scale; ES: Effect size; GRADE: Grading recommendations, assessment, development and evaluation; HCP: Health care professional; IPDAS: International patient decision aids standard; KT: Knowledge translation; OMRU: Ottawa model of research use; PDF: Portable document format; PtDA: Patient decision aid; RC: Research coordinator; RCT: Randomized controlled trial; RFA: Refractory angina; TAP: Treatment acceptability and preference questionnaire; TRIAGE: Technique for research of information by animation of a group of experts.
